#### Biological tests and biological collection

Standard of care will be done by assessing from blood: CBC-platelets, sodium, potassium, ALKP, ASAT, ALAT, GGT, total bilirubin, creatinin, albumin, CRP and TSH.

Optional specific blood samples (about 15 mL) for the further research will be collected at T0, T3, T6 for constitution of a biobank of PBMC, serum and plasma from blood samples of patients who have provided additional specific informed consent. Thus, at each collection time, 2 CPTTM (2X4 mm) and 1 BD vacutainer serum tube (5 mL). The CPT samples will be immediately sent to the Inserm U1245 laboratory (Rouen, France) for PBMC and plasma preparation under sterile condition while serum will be collected after centrifugation (3000 rpm, 10 min). PBMC will be stored in liquid nitrogen while plasma and serum will be kept frozen at − 80 °C.

These anonymized samples will be used for further hormonal, cytokine and genetic analyses. The samples will be stored in a secure area (CBG laboratory, Inserm research Unit, Rouen) with restricted access in accordance with the regulations in force.

### Statistical design overview

#### Sample size determination

To our knowledge, there is no published study about the estimation of the incidence of cognitive impairment in cancer patients treated with immunotherapy. We propose to carry out the present study, assuming that about 50% of the patients will develop cognitive impairment under immunotherapy. Using a 95% confidence interval with a width of 0.2 for small sample, it is necessary to include 93 assessable patients. To take into account lost to follow-up, we plan to enrol 7 additional patients, for a total of 100 patients.

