### Primary outcome

The primary objective of this study is to prospectively assess the incidence of cognitive impairment and cognitive complaints among cancer patients naïve for immunotherapy without concomitant anti-cancer treatment. The primary endpoint is the proportion of patients treated by immunotherapy who will experience a decline in cognitive performances (at least for one cognitive domain) or in MoCA score within 3 months after inclusion. It will be presented with its exact confidence interval at the 95% confidence level.

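### The 93 patients are sized for a 95% interval 0.2 wide at 50% incidence, but the exact interval named for the primary endpoint is about 0.21 wide there

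*Protocol article*

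**What the plan says.** Two sections of the protocol article bear on the same quantity, the proportion of patients with cognitive decline within 3 months.

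- **Sample size determination.** The calculation proceeds by "assuming that about 50% of the patients will develop cognitive impairment under immunotherapy", and then: "Using a 95% confidence interval with a width of 0.2 for small sample, it is necessary to include 93 assessable patients". The allowance for loss to follow-up is added on top: "we plan to enrol 7 additional patients, for a total of 100 patients". Apart from the remark about small samples, no interval method is given.
- **Primary outcome.** Of the primary proportion the article says: "It will be presented with its exact confidence interval at the 95% confidence level".

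The Statistical analyses section does not connect the two statements.

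**The concern.** The study is a single cohort and its primary analysis is estimation. No hypothesis or power is stated for the primary endpoint, so the interval width is the only quantitative justification for 93 and 100 patients. For that justification to hold, the width has to be the width of the interval that will be reported.

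Exact binomial intervals are generally wider than score-type intervals at the same sample size. If 93 came from a score-type formula, the reported interval will be wider than the plan states when the result is near the assumed 50%. A reader who checks the result against the plan would then find that the planned precision was missed, although enrolment went as intended.

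**Working it through.** **Inputs.** Assumed incidence p = 0.5, confidence level 95% two-sided (z = 1.96), target full width 0.2, 93 assessable and 100 enrolled patients (all from Sample size determination); exact interval (Primary outcome).

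**Step 1: reproduce 93.** At p = 0.5 the Wilson score interval has width z / √(n + z²). Setting this to 0.2 gives

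n = (1.96/0.2)² − 1.96² = 96.04 − 3.84 = 92.2, rounded up to 93.

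The width is 0.2002 at n = 92 and 0.1992 at n = 93, so 93 is the minimum. Agresti-Coull gives the same number. Other methods do not reach 0.2 at 93:

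| Interval | Width at n = 93, p ≈ 0.5 | Smallest n for width ≤ 0.2 |
|---|---|---|
| Wilson, Agresti-Coull | 0.1992 | 93 |
| Logit | 0.2005 | 94 |
| Jeffreys | 0.2006 | 94 |
| Mid-P | 0.2017 | 95 |
| Wald | 0.2032 | 97 |
| Clopper-Pearson (exact) | 0.2110 | 104 |

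So 93 is a correct figure for a Wilson-type interval.

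**Step 2: width of the exact interval.** For x events in n patients, the Clopper-Pearson limits are the 2.5% quantile of Beta(x, n − x + 1) and the 97.5% quantile of Beta(x + 1, n − x).

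| x/n | 95% limits | Width |
|---|---|---|
| 46/93 | 0.389 to 0.600 | 0.211 |
| 50/100 | 0.398 to 0.602 | 0.203 |
| 51/103 | 0.395 to 0.595 | 0.2003 |
| 52/104 | 0.400 to 0.600 | 0.1993 |

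At n = 93 the half-width is 0.211/2 = 0.106, against the intended 0.100. At n = 100 it is 0.203/2 = 0.102. Averaged over the binomial distribution at p = 0.5, the expected width is 0.210 at n = 93 and 0.202 at n = 100.

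**Step 3: where the shortfall occurs.** The exact width depends on the observed count.

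- n = 93: above 0.2 for 32 to 61 events (34% to 66%). At 31/93 it is 0.1997.
- n = 100: above 0.2 for 41 to 59 events (41% to 59%). At 40/100 it is 0.1995.

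If the true incidence is 50%, the chance of an exact interval no wider than 0.2 is about 0.2% at n = 93 and about 6% at n = 100.

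**Step 4: other meanings of exact.** The article does not say which exact method is meant. The Sterne and Blaker intervals are also wider than 0.2 at n = 93 (0.205 and 0.206) and at n = 100 (0.2006 and 0.2018), so the mismatch remains. The figure of 104 is specific to Clopper-Pearson.

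**The case against.** The strongest reply is that the difference is too small to matter. The target is given to one decimal, around an incidence of about 50%, and both 0.211 and 0.203 round to 0.2. About half a percentage point per side changes no conclusion in a cohort without a decision threshold. This stands as a limit on the weight of the point. It does not remove it: 93 was evidently obtained by treating 0.2 as a hard limit, since 92 patients miss it by only 0.0002 under Wilson, and a gap of 0.011 is much larger than that.

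Second, 50% is a planning value. The article says that no published incidence exists, and 50% is the worst case for width. Its Background cites 15-25% decline with chemotherapy and 31% with an antiangiogenic treatment. At a true 25% or 31%, the expected exact width with 93 patients would be 0.183 or 0.195, within target. This also stands, although those rates come from other treatments and perhaps other definitions of decline. The precision claim is nevertheless made at 50%, and at 50% it is not met.

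Third, Wilson is inferred, because the article names no sizing method. That is correct. The point does not depend on it, because the exact interval exceeds 0.2 whichever formula produced 93.

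A reader might go further and infer that 93 is miscalculated, that the trial is too small, or that the primary analysis is invalid. The documents support none of these. The figure of 93 is reproduced exactly by a recognised method. The precision lost is small. The exact interval remains valid, with coverage of at least 95%.

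**Conclusion.** The point holds in a limited form. The sample size section and the primary outcome section rest on different intervals, and the precision stated in the first is not delivered by the analysis named in the second at the plan's own assumed incidence. This is an inconsistency to correct in the text. It is not a defect in the size of the trial or in the choice of analysis.

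The conclusion rests on reading width as full width, as the article's wording indicates, and on an observed proportion in the middle range. The exact sizes quoted assume Clopper-Pearson; under the other exact methods checked, the excess is smaller but still present at both 93 and 100.

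**What to change.** Keep the exact interval as primary, and reword the precision statement in Sample size determination to say that, if the incidence is 50%, the expected width of the exact 95% confidence interval is about 0.21 with 93 assessable patients and 0.203 with 100. Naming the exact method (for example Clopper-Pearson) in the same sentence would settle which interval is meant. A Wilson interval can be shown alongside as supportive.

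Making Wilson the primary interval would also align the two sections, but it gives up guaranteed coverage of at least 95% in a study already under way in order to match a planning figure. Restating the width avoids that trade-off.

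The cost is one sentence and a slightly less favourable stated precision. No extra patients are needed.

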#### Statistical analyses

Exploratory analyses of the data will provide, for quantitative variables, the mean, standard deviation, median, quartiles, and number of missing values; for qualitative variables, we will calculate the frequencies and their 95% confidence intervals. The demographic and clinical characteristics of the patients will be described. The estimation of the incidence of the cognitive impairment will be described according to the characteristics of the patients. When possible, statistical tests (non-parametric) will be used to estimate the association between different factors and the occurrence of cognitive impairment. A two-sided alpha risk of < 0.05 will be considered significant. We will measure the association between cardiac variability, hemispheric lateralization and psychological variables on the one hand, and cognitive alterations on the other, using a hierarchical regression analysis, after taking into account the initial cognitive assessment and prognostic factors (age, cancer stage, etc.).

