### Secondary outcomes

The secondary objectives are to assess:The relationship between objective cognitive impairment and anxiety, depression, and fatigue,The relationship between objective cognitive impairment and cognitive complaints,The relationship between cognitive functioning (objective and subjective) and clinical characteristics such as cancer stage, comorbidities, comedications…The relationship between cognitive impairment and biological data,The incidence or the severity of cognitive impairment induced by immunotherapy based on neurophysiological measures and cognitive ones.

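### Factors outside the hierarchical regression are tested only against yes/no impairment, which discards about 36% of the information in a continuous score at the planned 50% rate

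*Protocol article*

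**What the plan says.** Three statements in the protocol article bear on this point.

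- **Statistical analyses, general factors.** Where possible, "statistical tests (non-parametric) will be used to estimate the association between different factors and the occurrence of cognitive impairment". The criterion is "A two-sided alpha risk of < 0.05 will be considered significant".
- **Statistical analyses, regression.** The section continues: "We will measure the association between cardiac variability, hemispheric lateralization and psychological variables on the one hand, and cognitive alterations on the other". The method named for this is hierarchical regression, adjusted for baseline cognition and for prognostic factors such as age and stage. The scale of the cognitive outcome in this regression is not given.
- **Primary outcome.** The only definition of decline is "a decline in cognitive performances (at least for one cognitive domain) or in MoCA score within 3 months after inclusion", which is a yes/no label over several domains and the MoCA.

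The first objective under Secondary outcomes is the "relationship between objective cognitive impairment and anxiety, depression, and fatigue". The others cover cognitive complaints, clinical characteristics, biological data and the neurophysiological measures. The objective on clinical characteristics is about cognitive functioning, both objective and subjective. The neurophysiological objective mentions severity as well as incidence.

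Table 1 schedules the MoCA, the main test battery and the questionnaires at baseline (T0), 3 months (T3) and 6 months (T6). Its footnotes restrict patients with a below-threshold baseline MoCA to the MoCA and questionnaires at every visit.

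**The concern.** Most secondary objectives ask about association, and the sample was sized only for the width of one confidence interval. Reducing each patient's scores to impaired or not impaired removes the size of the change and gives a memory-only decliner the same label as an executive-only decliner. The occurrence tests, as described, also make no adjustment for the baseline score.

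For factors that the regression does not cover, this is the only named analysis. Moderate associations that the collected scores could show may be missed, and a null result may then be read as evidence of no association.

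**Working it through.** **Inputs from the protocol article.** 93 assessable patients, 50% expected impairment, 95% interval of width 0.2 (Sample size determination); two-sided alpha 0.05 (Statistical analyses).

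**Assumptions, not in the document.** Factor and cognitive change are normal with correlation r of 0.2 to 0.4. Splits of 30% and 15% are alternatives to 50%. They are plausible because the Background cites decline in 15-25% of patients after chemotherapy and 31% after antiangiogenic treatment.

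**Step 1: the plan's own figure.** The Wilson interval at p = 0.5 has half-width z / (2·√(n + z²)). Setting this to 0.1 gives n = z²·0.25/0.1² − z² = 96.04 − 3.84 = 92.20, rounded up to 93. The stated 93 is reproduced. It concerns precision of the proportion only.

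**Step 2: information kept after splitting a normal score.** Efficiency = φ(c)² / [p(1 − p)], where c is the cut at proportion p.

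- p = 0.50: 0.3989² / 0.25 = 0.637, a loss of 36%; effective n = 0.637 × 93 ≈ 59
- p = 0.30: 0.3477² / 0.21 = 0.576, a loss of 42%
- p = 0.15: 0.2332² / 0.1275 = 0.426, a loss of 57%

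**Step 3: power.** Power = Φ(atanh(r)·√(n − 3) − 1.96), with r multiplied by √efficiency for the split score. For r = 0.3, the continuous score gives 0.3095 × 9.487 = 2.936, and Φ(0.976) = 84%. At the 50% split, r becomes 0.3 × 0.798 = 0.239, the product is 2.316, and Φ(0.356) = 64%.

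| r | Continuous | 50% split | 30% split | 15% split |
|---|---|---|---|---|
| 0.2 | 48.5% | 33.2% | 30.5% | 23.8% |
| 0.3 | 83.6% | 63.9% | 59.4% | 46.9% |
| 0.4 | 98.0% | 88.0% | 84.4% | 71.8% |

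Simulation at r = 0.3 agrees: about 84% for the Pearson test on the continuous score, and 63%, 58% and 46% for the Mann-Whitney test on the three splits. The Spearman test on the continuous score keeps about 81%, so the loss comes from the split and not from using ranks.

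**Step 4: the composite label.** The endpoint is positive if any of four domains or the MoCA declines. This was simulated with five changes intercorrelated 0.3 (assumed), a 50% overall rate and n = 93. The continuous column tests five scores with Bonferroni at 0.01 each.

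| How the factor acts | Yes/no label | Five continuous scores |
|---|---|---|
| r = 0.3 with one domain, 0 with the others | 8-9% | 65-67% |
| r = 0.3 with one domain, 0.09 (0.3 × 0.3) with the others | about 25% | about 67% |
| r = 0.3 with all five | 84-85% | 96-97% |

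The composite therefore does badly for domain-specific effects and moderately for common ones.

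**The case against.** **The regression already adjusts for baseline.** This stands. A reader might infer that every association analysis is unadjusted and ignores the T0 score. The document does not support that. The hierarchical regression takes the initial cognitive assessment and prognostic factors into account, and its psychological variables most naturally include anxiety and depression, perhaps fatigue. The point is confined to the factors it does not name, plus its unstated outcome scale.

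**Half the power is lost.** A reader might infer this too, but at the plan's own 50% rate the relative loss is 10-32% over r = 0.2 to 0.4. Half is approached only near a 15% split with r of 0.2 to 0.25, or under particular composite structures.

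**The objectives mostly ask about impairment, so a yes/no outcome fits.** This is partly right, and it is why the occurrence tests should stay. It does not fit the wording on functioning and severity.

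**Outcome scale and visits may be set in the full protocol or SAP.** This is fair for the regression's outcome and for use of the 6-month data, so neither is called an omission here. The occurrence tests, by contrast, are a stated choice.

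**Several continuous outcomes cost alpha.** This is true. One score tested at 0.01 with r = 0.3 has power Φ(2.936 − 2.576) = 64%, the same as a single split score at 0.05. But the actual label is a composite, and Step 4 shows five corrected continuous tests ahead of it in all three scenarios.

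**Below-threshold patients have no domain scores.** This stands as a small cost. They still contribute to a MoCA model.

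**Conclusion.** The concern holds within limits. For biological data, clinical characteristics other than as covariates, and cognitive complaints (unless these count as psychological variables), the only named analysis is a non-parametric test on a yes/no label. At the planned 50% rate this discards about 36% of the information in a normal score. Power falls from about 84% to 64% at an assumed correlation of 0.3, and further at lower decline rates or for effects on one domain.

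The 36% rests on normality and on treating the label as a cut of one score. The power figures also rest on the assumed correlation and a continuous factor, whereas some listed factors are categorical. The composite results depend on the assumed intercorrelation and on how the factor acts. The primary endpoint and its sample size are unaffected.

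**What to change.** Keep the binary proportion as the primary endpoint and the occurrence tests as supportive analyses. Then:

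1. For the factors outside the regression, add a linear model of each continuous T3 score (MoCA and domains) on the factor, adjusted for the T0 score. Alternatively, use a mixed model with T3 and T6 as repeated outcomes and T0 as covariate, which also keeps patients who miss one of the two visits. Report slopes with 95% confidence intervals.
2. State that the hierarchical regression uses the continuous score as its outcome.
3. State how multiplicity over the scores is handled, or name a composite mean score as the main outcome. A mean suits effects common to all domains but dilutes a domain-specific one.
4. State that patients below the baseline MoCA threshold contribute to the MoCA model only.

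The cost is wording and some analysis time. No new data, visits or patients are needed.

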### Ancillary pre-clinical study

A complementary pre-clinical study will be conducted using mouse behavioural preclinical models. C57B/l6 mice bearing different immunogenic murine cancers (melanoma B16F10 and B16F10-ova cells; murine colon carcinoma MC38 cells) will be treated by three injections (1/week) of murine control IgGs, anti-PD-1 or anti-PDL-1 from day 3 after cancer cells inoculation. Activity, cognitive performances and emotional reactivity using a battery of behavioral tests will be assessed during the course of the treatment. Given the neuropsychological characteristics of cancer patients and the neurobiological impairment sometimes observed in treated patients, our behavioural analysis will mainly focus on tests that highlight an alteration of the hippocampus and the pre-frontal cortex. For emotional reactivity, tail suspension (TST, FST, elevated cross maze; cognition, Morris pool, object recognition), behavioural tests will be performed over 5 weeks overall.

In order to investigate whether certain alterations in cognitive functions or emotional responses are associated with neuro-inflammation and/or changes in the cerebral vascular network, the levels of intraparenchymal cytokines TNF-α, IL-1β, IL-17, IL-6 and INF-γ will be analysed by Elisa and quantitative PCR (one cerebral hemisphere will be sampled for protein lysate preparation, and the other hemisphere for mRNA preparation). From fresh brain samples including choroid plexuses, leukocytes will be isolated by flow cytometry using antibodies myeloid cells (resident microglia and macrophages) and against T lymphocytes (CD4 and/or CD8), NK (DC56) and B cells (CD19), as well as granulocytes and monocytes. By immunohistochemistry, microglial reactivity and reactive astrogliosis will also be investigated in particular in the vascular network, in the hippocampus and/or the pre-frontal cortex. Neuronal degeneration using Fluorojade-c + labelling in the brain area innervated at least in part by the vagus nerve, in mice bearing the most immunogenic B16F10-Ova and MC38 cancers and treated by ICI, will be tested. At the vascular level, by double labelling, endothelial reactivity will be checked using antibodies directed against adhesion proteins ICAM, VCAM, selectins and certain integrins, and the sites of leukocyte infiltration will also be sought at the edges of the cerebral vasculature.

Then, from plasma samples and brain extracts, we will search for plasma biomarkers (cytokine assays) and neurobiological mechanisms such as cerebral vascularisation, neuro-inflammation (Western blot, flow cytometry, immunohistochemistry) and electrical activities (patch-clamp on slice) associated with potential disturbances of emotion and/or cognitive functions in animals treated with immunotherapy targeting PD-1 or PD-L1.

### Data management

A Web Based Data Capture (WBDC) system will be used for data collection and query handling. The investigator will ensure that data are recorded on the eCRFs as specified in the study protocol and in accordance with the instructions provided.

The investigator ensures the accuracy, completeness, and timeliness of the data recorded and of the provision of answers to data queries according to the Clinical Study Agreement. The investigator will sign the completed eCRFs. A copy of the completed eCRFs will be archived at the study site.

### Withdrawal from study

The reasons for why a patient may discontinue to participate to the study include the following circumstances:Immunotherapy treatment discontinuation, whatever the reason (unacceptable toxicity, disease progression…),Patient’s decision (the data already collected during the search can be kept and exploited unless the patient opposes it),Intercurrent illness or other reason that requires stopping participation to the studyPatient lost to view,Investigator’s decision.

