Nevertheless, by modifying the immune balance, these treatments can be associated with the appearance of neurological toxicities (e.g. encephalopathy) and autoimmune side effects due to the lifting of the brake on the immune system induced by these molecules (mainly anti-CTLA-4 and anti-PD-1) [19]. These side effects are rare (1%) but probably underestimated and potentially serious [20]. The most frequent autoimmune side effect in the central nervous system is hypophysitis (18% of patients treated with anti-CTLA-4) with grade 3 or higher toxicity in 5% of cases. The most frequent manifestation is fatigue, which can lead to concentration problems. For anti-PD-1, specific autoimmune side effects are rare but severe when they occur [21]. These side effects usually occur within the first 2 months of treatment. However, due to the recent nature of immunotherapy, little is known about its side effects and their impact on quality of life [13, 22]. To date, only the findings from one pilot study were published on the impact of immunotherapy on cognition in patients treated for cancer [23]. In this small sample, cognitive decline, only assessed by cognitive screening tests, was more related to chemotherapy rather than immunotherapy. Thus, these first results should be completed in further studies with the use of several cognitive tests in a large sample, addressing a population naïve for immunotherapy without concomitant anti-cancer treatment.

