### Study assessments

The study flow-chart and overview of study assessments (cognitive tests, self-report questionnaires for quality of life evaluation, and biological tests) are indicated in Fig. 1 and Table 1. Assessments will be conducted, once signed the consent form, at inclusion - baseline (T0) - (before the start of immunotherapy or within 7 days after the start of immunotherapy), 3 months (±15 days; T3), and 6 (±15 days; T6) months after the immunotherapy initiation.

**Table 1 Tab1:** Overview of the Cog-Immuno study assessments

Assessment	T0^c^	T3 3 months	T6 6 months
**Signed informed consent**	✓		
**Cognitive assessment**^**a**^			
-MoCA^2^	✓	✓	✓
If normal MoCA score^b^:			
-Hopkins verbal learning test	✓	✓	✓
-Digit span (WAIS-IV)	✓	✓	✓
-Trail Making test	✓	✓	✓
-Stroop	✓	✓	✓
-Symbol search (WAIS-IV)	✓	✓	✓
-Verbal fluencies	✓	✓	✓
-Cancellation (WAIS-IV)	✓	✓	✓
-Line bissection	✓		

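### Stopping immunotherapy for any reason is a permitted ground for leaving the study, which exposes the 3-month primary incidence to selective loss of outcome data

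*Protocol article*

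**What the plan says.** All references are to the Protocol article.

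- **Withdrawal from study.** The list opens with "The reasons for why a patient may discontinue to participate to the study include the following circumstances", and its first item is "Immunotherapy treatment discontinuation, whatever the reason (unacceptable toxicity, disease progression". Patient decision, intercurrent illness, loss to view and investigator decision are separate items. Keeping data already collected is mentioned only beside patient decision. Nothing says that assessments continue once treatment has stopped.
- **Primary outcome.** "The primary endpoint is the proportion of patients treated by immunotherapy" who show a "decline in cognitive performances (at least for one cognitive domain) or in MoCA score within 3 months after inclusion". The population is defined by having been treated, not by still being on treatment at 3 months.
- **Study assessments.** After baseline, visits are at "3 months (±15 days; T3), and 6 (±15 days; T6) months after the immunotherapy initiation". Only T3 can supply the primary endpoint.
- **Immunotherapy in oncology.** On the timing of toxicity: "These side effects usually occur within the first 2 months of treatment".
- **Sample size determination.** 93 assessable patients are required. "To take into account lost to follow-up, we plan to enrol 7 additional patients, for a total of 100 patients".

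**The concern.** Taken together, these sections let a patient who stops treatment in the first weeks leave before the one measurement that feeds the primary endpoint. The two reasons named for stopping, toxicity and progression, are plausibly related to cognition. The background itself says that fatigue from immune toxicity can disturb concentration. Whether T3 is missing may therefore depend on the outcome.

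This is a question of data collection. An analysis plan can bound or model missing T3 results, but it cannot recover assessments that were never made. At stake is whether the sole primary estimate describes everyone who started immunotherapy, as the endpoint is worded, or leans towards those who tolerated it and did not progress early. A second issue is precision: the 7 extra patients are described only as cover for loss to follow-up, which the withdrawal list treats as a different reason from stopping treatment.

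**Working it through.** **1. Reproduce the plan's figure.** Inputs from Sample size determination: incidence 50%, 95% confidence, total width 0.2. A Wilson-type interval at p = 0.5 has width 2z√(0.25/(n + z²)). Setting this to 0.2 gives n = z²×0.25/0.1² − z² = 96.04 − 3.84 = 92.2, rounded up to 93. Then 93/(1 − 0.07) = 100. Both stated numbers reproduce, and neither is in dispute.

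**2. Timing.** Side effects are placed mostly in months 0-2, and T3 falls at 3 months ±15 days. A patient who stops for an early side effect therefore does so before T3.

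**3. Effect on the estimate.** Let d be the share of treated patients without T3 because treatment stopped, p_c the incidence in those assessed, and p_s the incidence in those not assessed. The incidence in all treated patients is (1 − d)p_c + d·p_s, so the observed figure differs from it by d(p_c − p_s). The documents give neither d nor p_s, so the following are assumptions.

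| d | p_s − p_c | Understatement | If 40% observed, all-treated incidence |
|---|---|---|---|
| 20% | 20 points | 0.2×0.20 = 4 points | 44% |
| 20% | 30 points | 0.2×0.30 = 6 points | 46% |
| 30% | 20 points | 0.3×0.20 = 6 points | 46% |
| 30% | 30 points | 0.3×0.30 = 9 points | 49% |

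If p_s = p_c the error is zero. If p_s were 20 points lower than p_c, the estimate would be overstated by 4 points (d = 20%) or 6 points (d = 30%). With only the planned 7% missing, a difference of 30 points gives 0.07×0.30 = 2.1 points.

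**4. Bounds without assuming p_s.** Suppose 50% of assessed patients decline. The all-treated incidence then lies between 0.5(1 − d) and 0.5(1 − d) + d:

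- d = 7%: 46.5% to 53.5%
- d = 20%: 40% to 60%
- d = 30%: 35% to 65%

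At d = 20% this range, before any sampling error, is as wide as the whole planned interval.

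**5. Precision.** The analysis is to use an exact interval, so exact widths near 50% are compared with each other:

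| Assessable | Exact 95% width | Change from n = 93 |
|---|---|---|
| 93 | 0.211 | – |
| 80 | 0.228 | +0.017 |
| 70 | 0.244 | +0.033 |

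To keep 93 assessable, enrolment would have to be 93/0.8 = 116.25, so 117, or 93/0.7 = 132.9, so 133.

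**The case against.** The strongest case on the other side has five parts.

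- **The rule is permissive.** The list says that a patient may leave. It does not require it, and no section defines the analysis set. A reader might infer that the incidence is biased and that the analysed patients will be those still on treatment at 3 months. The text does not support that; it supports exposure to bias. Permissive wording does not remove the problem, however, because retention could then differ between centres.
- **Toxicity alone does not give 20-30% stopping.** The background calls these side effects rare (1%), though probably underestimated. Its largest figure is hypophysitis in 18% under anti-CTLA-4, with grade 3 or higher toxicity in 5%. Having a side effect is also not the same as stopping treatment. Much of the assumed range would have to come from progression, for which the article gives no early rate and no link to cognition. This stands, and it is why the sizes are illustrations.
- **The shortfall is not established.** A reader might conclude that 93 assessable patients are unlikely to be reached. Without a discontinuation rate the documents cannot show that.
- **Patients who stop may start another therapy before T3.** The objective concerns immunotherapy without other cancer treatment alongside, and the background reports that chemotherapy and antiangiogenic drugs can themselves affect cognition. A single estimate that ignores treatment status would mix these effects. This stands and shapes the fix.
- **The full protocol may say more.** The article condenses it, and bounds and sensitivity analyses normally belong to the analysis plan. That lowers certainty about what is done in practice, but the withdrawal rule as stated still conflicts with the endpoint population.

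**Conclusion.** The point holds as one of exposure. The withdrawal list makes stopping treatment a stand-alone ground for leaving, the endpoint is defined over all treated patients, and the only visit that supplies it comes after the period in which side effects are said to occur. Outcome data can be lost selectively, and later analysis cannot restore them.

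The direction is understatement if those who stop decline more often, which is plausible but not shown. The 4-9 points and the widening of the exact interval from 0.211 to 0.228-0.244 rest entirely on an assumed 20-30% without T3; the 4-9 points also assume a 20-30 point difference in decline. The calculation of 93 and 100 is sound. What is unclear is whether the 7 extra patients are meant to cover those who stop treatment.

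**What to change.** 1. In Withdrawal from study, separate stopping immunotherapy from leaving the study. State that the scheduled T3 and T6 assessments continue after treatment stops unless consent is withdrawn or the patient cannot be assessed. This concerns data collection only and changes no treatment rule.
2. At T3, record whether the patient is still on immunotherapy and whether any new cancer therapy has started, with dates.
3. Estimate incidence over all treated patients with a T3 assessment. Beside it, give an estimate restricted to patients still on immunotherapy or without new cancer therapy.
4. Report missing T3 by reason, with best-case and worst-case bounds as in step 4 of the working.
5. Reconcile Primary outcome, Sample size determination and Withdrawal from study on whether the 7-patient allowance covers patients who stop treatment.

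**Cost.** A short amendment and matching analysis wording, plus one or two already scheduled assessments in patients who have stopped treatment. Some T3 results will reflect subsequent therapy, which the second estimate addresses. The article describes the study as ongoing, so only T3 visits not yet due can still be saved.
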